### Sample Size Calculation

Based on previous research [14], a clinically meaningful change in exercise tolerance on the BCBT has not been formally defined using a minimal clinically important difference. Therefore, a clinically meaningful difference was prespecified based on a combination of the empirical variability and functional interpretation of the test. In the original BCBT validation study, patients demonstrated a mean time to symptom provocation of 14.6 (SD 6.0) minutes, whereas healthy controls showed a mean time of 27.2 (SD 5.2) minutes, indicating a disease-related impairment of approximately 12‐13 minutes. A between-group difference of 6 minutes was therefore defined as clinically meaningful, corresponding to approximately half of this observed deficit, 1 SD of patient performance, and completion of 3 additional workload stages on the BCBT, which progresses in 2-minute increments.

Assuming a common SD of 6 minutes, a between-group difference of 6 minutes corresponds to a standardized effect size of 1.0. With a 2-sided type 1 error rate of 5% and a statistical power of 90%, at least 22 participants were required in each group.

Relevant uncertainty measurements for BBB permeability, spectroscopy, lactate, and diffusion were already available for subproject 3, for both paired and unpaired data. Specifically, for BBB permeability, we set the standard difference to 1 (effect size) based on our previous investigation of the reproducibility of BBB permeability [45], and setting the significance level to 1% and the power to 90%, 27 participants were required in each group. Considering a tentative dropout rate of 30%, we aimed to recruit a total of 70 participants in the study.

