## Methods

### Trial Design

This study protocol describes the design of the Rehabilitation in Postconcussion Symptoms (REPCon) project, an assessor-blinded, parallel-group, randomized controlled superiority trial. Adult patients with PPCSs showing symptoms for more than 4 weeks after the initial mTBI were randomized in a 1:1 ratio to either a control group (CG) or a TG. Participants in both groups continued their usual daily activities and received usual care as delivered in routine clinical practice. In accordance with the pragmatic design of the trial, usual care is not standardized and reflects current real-world management. Usual care may include follow-up by a general practitioner or medical specialist, symptom monitoring, pharmacological treatment (eg, for pain or sleep disturbances), advice regarding activity modification and return to activity, and referral to allied health services such as physiotherapy or psychology, as clinically indicated. Participants allocated to the TG additionally received a supervised graded physical exercise program, as described below. Concomitant care and co-interventions were discouraged in both groups, and any changes were reported to the study group. The only protocol-mandated difference between groups was the addition of a supervised exercise intervention in the TG. The study includes the following four subprojects: (1) qualitative evaluation, (2) physiological evaluation, (3) neurofunctional evaluation, and (4) comprehensive evaluation. The primary outcome is improvement in exercise tolerance measured as time to symptom exacerbation during the graded aerobic exercise testing protocol 12 weeks after baseline [14]. The secondary outcomes include differences in symptom complexity, dynamic gait, fatigue, headache, and the findings of a range of other neurophysiological tests and functional abilities between the TG and CG at 12 weeks after baseline, as well as the normalization of quantitative MRI measures in the TG and the between-group differences in these measures. The tertiary outcome is the triangulation of data from the subprojects to provide a nuanced and integrated understanding of biology, physiology, and patient perceptions of PPCSs, thereby potentially improving clinical recommendations. The trial has been registered in the ClinicalTrials.gov repository (NCT05785000). The findings will be reported in accordance with the SPIRIT (Standard Protocol Items: Recommendations for Interventional Trials) guidelines [20,21]. The SPIRIT checklist is provided in Checklist 1.

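### Seventy recruits with 30% dropout leave 24–25 per group for the BBB comparison, not the 27 required, and 27 itself gives 90% power only under an undeclared one-sided 1% test

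*Protocol article*

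**What the plan says.** The protocol article's Sample Size Calculation section contains two calculations. For the primary outcome, time on the Buffalo Concussion Bike Test (BCBT), it takes a difference of 6 minutes and an SD of 6 minutes: "With a 2-sided type 1 error rate of 5% and a statistical power of 90%, at least 22 participants were required in each group".

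For BBB permeability it also uses a standardized effect of 1, but at a stricter level: "setting the significance level to 1% and the power to 90%, 27 participants were required in each group". That sentence does not say whether the 1% is one- or two-sided, nor which two groups are compared. The sentence before it says that variability estimates exist "for both paired and unpaired data".

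The section closes: "Considering a tentative dropout rate of 30%, we aimed to recruit a total of 70 participants in the study". Under Trial Design, patients "were randomized in a 1:1 ratio to either a control group (CG) or a TG", so 70 means 35 per group.

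**The concern.** The sentence on dropout directly follows the BBB figure, and BBB is the larger of the two requirements. A reader will therefore take 70 as the number that secures 27 per group after 30% loss. It does not.

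Separately, the paragraph before declares a two-sided test, whereas 27 looks too small for a two-sided 1% test with 90% power.

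At stake is the power claimed for one secondary outcome. Under Secondary Outcomes, BBB change is to be assessed by trial arm as well as against healthy controls. A result in either direction will be read against the stated 90%.

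**Working it through.** **Inputs** (Sample Size Calculation and Trial Design): standardized effect d = 1; level 1%; power 90%; 27 per group; dropout 30%; total 70; allocation 1:1. Sidedness is not given, so both readings are shown.

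**1. Reproducing the 27.** The normal formula for two independent groups is n per group = 2(z_α + z_β)²/d², with z_β = 1.282 for 90% power.
- One-sided 1%: 2(2.326 + 1.282)² = 26.03, rounded up to **27**. This matches the article. The t-based number is 28.
- Two-sided 1%: 2(2.576 + 1.282)² = 29.76, rounded up to **30**. The t-based number is 32.
- A paired design does not give 27: it needs 16 (one-sided) or 19 (two-sided).

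The primary calculation, by contrast, is reproduced two-sided: 2(1.960 + 1.282)² = 21.01, rounded up to 22. The one-sided version would be 18. With the stated level and power, the two adjacent figures therefore follow from different conventions.

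**2. Dropout step.**
- Required completers: 2 × 27 = 54.
- Completers from 70 at 30% loss: 70 × 0.70 = 49, or 24.5 per group.
- Recruits needed for 54 completers: 54/0.7 = 77.1, rounded up to 78.
- Loss that 70 can absorb: 1 − 54/70 = 22.9%.
- For comparison, 54 × 1.3 = 70.2, which is close to the planned total.

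**3. Power at d = 1 and 1% level (noncentral t).**

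| Per group | One-sided | Two-sided |
|---|---|---|
| 27/27 | 89.5% | 83.7% |
| 24/25 | 85.8% | 78.8% |

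The normal approximation gives 91.1% and 86.4% at 27 per group, and about 87–89% and 81–83% at 24–25 per group. At the planned number of completers, power is below 90% in every case.

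**4. Primary outcome.** 44/0.7 = 62.9, so 63 recruits suffice and 70 exceeds this. At 24/25 per group, power at two-sided 5% is about 93%.

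**The case against.** The strongest objection concerns the 27. A reader might infer that it is simply an arithmetic error. The article does not support that: the BBB sentence declares no sidedness, and a one-sided 1% normal calculation gives exactly 27. A one-sided reading is also compatible with the Objectives section, which hypothesizes increased permeability in patients. This objection stands. What remains is that no one-sided test is declared anywhere in the article and that the neighbouring calculation is two-sided, so the reader cannot tell which test has the stated power.

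A reader might also infer that the authors multiplied 54 by 1.3. The closeness of 70.2 to 70 suggests this, but the article shows no inflation formula, so it is only a possible explanation. The shortfall does not depend on it.

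Third, the contrast is not named. If 27 refers to patients versus healthy controls at baseline, follow-up dropout among patients does not reduce that comparison, and the article does not give the number of healthy controls. This stands as a limit: the power loss applies to the training-versus-control comparison at 12 weeks. The step from a per-group number to a randomized total of 70 points to that contrast without settling it.

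Fourth, BBB is secondary, the Statistical Analysis section treats the further tests as hypothesis-generating, the 30% is called tentative, and enrolment has closed. All of this lowers the severity. It does not make 49 completers equal to 54.

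Finally, it is tempting to object that the 1% level does not reappear in the BBB analysis text. That is no finding: a condensed article commonly leaves such thresholds to the full plan.

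**Conclusion.** The point holds in two parts, with moderate severity.

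First, on the article's own figures, 70 recruits with 30% dropout do not deliver 27 per group. They leave 24–25, which is 5 completers short in total. For a training-versus-control BBB comparison at 12 weeks, the stated 90% power becomes about 86% (one-sided 1%) or about 79% (two-sided 1%). This assumes a true standardized effect of 1, independent groups, a t test without covariates, and losses spread evenly between the arms. The Discussion accepts that some patients do not complete all MRI sessions, so the number with BBB data could differ from overall trial retention; the article gives no figure for this.

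Second, 27 per group has the stated power only under a one-sided test that is not declared. If the test is two-sided, 27 gives about 84%, and 90% needs 30 (normal) to 32 (t) per group.

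A reader might infer that the whole trial is too small. That does not follow: the primary outcome needs 22 per group and keeps about 93% power at 24/25.

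**What to change.** Correct the Sample Size Calculation text, without enrolling more patients:

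- State whether the 27 was calculated one- or two-sided, and whether it refers to training versus control or to patients versus healthy controls. The sponsor must supply what was actually used; it should not be chosen now that follow-up is complete and analysis is under way.
- State that 70 recruits with 30% loss leave 24–25 per group, and give the resulting power at effect size 1 for the training-versus-control comparison: about 86% one-sided or about 79% two-sided. Alternatively, say that 70 preserves 27 per group only if loss is at most about 23%.
- If the calculation was meant to be two-sided, correct 27 to 30 (normal) or 32 (t).
- Add that the primary outcome keeps its planned power.

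The cost is a few sentences and a less favourable power figure for one secondary outcome. Conduct, enrolment and the primary analysis do not change.

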### Statistical Analysis

The primary outcome of this RCT study is an increase in time to symptom exacerbation during the BCBT from before to after the 12-week intervention. To evaluate this effect while avoiding sensitivity to false-positive error from repeated measurements on the same participant, we will use a linear mixed model. To assess the effect of the intervention, a regressor indicating either pre- or postintervention (Time) and a regressor indicating group allocation (Group) will be included as fixed effects. Participant identification will be included as a random effect (*u*) to account for repeated measurements. Sex and age may influence these results, and they will be included as fixed effects. The additional effect of group allocation and pre- and postintervention on the results of the BCBT will be included as an interaction term (Group_i_ and Time_ij_). This interaction term will provide the main result of the RCT study. The model is formulated as follows:

$$\begin{array}{c} Y_{ij}=\beta_{0}+\beta_{1}{\text{Group}}_{i}+\beta_{2}{\text{Time}}_{ij}+\beta_{3}({\text{Group}}_{i}\times {\text{Time}}_{ij})\\ +\beta_{4}{\text{Age}}_{i}+\beta_{5}{\text{Sex}}_{i}+u_{i} \end{array}$$

where *Y* is the duration (in minutes) of exercise on the bicycle until symptom provocation and *β*s are regression coefficients, with *β*_3_ representing the primary result of the RCT. The subscript *i* denotes the subject, and the subscript *j* denotes pre- or postintervention measurement.

For MRI parameters, 2 main tests will be performed for the baseline data. These analyses will be repeated after the 12-week intervention period and will include the intervention as a regressor, as explained in the following text. At baseline, the CMRO2 level (overall oxygen consumption of the brain) between healthy control participants and patients with PPCSs will be tested using ordinary least squares regression adjusted for age and sex, with heteroscedasticity-consistent SEs to account for possible nonconstant error variance. To investigate whether the physiological response to hypoxic exposure differs between patients with PPCSs and healthy controls, we will test whether the change in CMRO2 from hypoxic exposure differs between the groups. Initially, we will assess differences at baseline (preintervention) using a mixed linear regression as follows:

$$\begin{array}{c} Y_{ij}=\beta_{0}+\beta_{1}{\text{Group}}_{i}+\beta_{2}{\text{SaO}}_{2,ij}+\beta_{3}({\text{Group}}_{i}\times {\text{SaO}}_{2,ij})\\ +\beta_{4}{\text{Age}}_{i}+\beta_{5}{\text{Sex}}_{i}+u_{i} \end{array}$$

where *Y*_*ij*_ denotes CMRO2, Group refers to either healthy controls or patients with PPCSs, and SaO2 is the actual oxygen saturation level in blood measured during the experiment (ie, during normoxia and hypoxia). Thus, we take the actual individual level of blood desaturation into account. The regression value *β*_3_ of the interaction term provides an inference regarding the patient’s ability to maintain CMRO2 under hypoxic stress conditions. After the 12-week intervention period, only patients will be tested for a possible change in their ability to maintain CMRO2 during the hypoxic exposure. Patients will be split according to group allocation (CG or TG), and the model is formulated as follows:

$$\begin{array}{c} Y_{ijk}=\beta_{0}+\beta_{1}{\text{Group}}_{i}+\beta_{2}{\text{SaO}}_{2,ijk}+\beta_{3}{\text{Time}}_{jk}\\ +\beta_{4}({\text{Group}}_{i}\times {\text{SaO}}_{2,ijk}\times {\text{Time}}_{jk})+\beta_{5}{\text{Age}}_{i}+\beta_{6}{\text{Sex}}_{i}+u_{i} \end{array}$$

where Time_ijk_ codes for pre- or postintervention (*k*) and Group codes for either the CG or TG, with the other parameters being as described above. The interaction term infers information on whether time (pre- or postintervention) has any impact on the group-specific CMRO2 response. Comparison of BBB permeability between patients with PPCSs and healthy controls will be performed using a linear regression model adjusted for age and sex, with heteroscedasticity-consistent SEs to account for possible nonconstant error variance. For exploratory regional analysis of BBB permeability across multiple brain parcels, Benjamini-Hochberg false discovery rate correction will be applied to control for multiple comparisons.

Structural equation modeling (SEM) and latent class analysis (LCA) will be used to identify latent variables and subgroups associated with PPCSs. Both approaches will be applied in an exploratory framework to generate hypotheses for future research. In the SEM analyses, observed variables will be treated as manifestations of an underlying normally distributed latent construct representing PPCS severity. The model will include the summed Rivermead score, time cycled and maximal workload during the BCBT, MRI-based CMRO2 measurements under normoxia and hypoxia, and BBB permeability. The latent variable will be scaled to the summed Rivermead score to facilitate interpretation. By integrating information across multiple domains, we aim to obtain a more comprehensive and sensitive representation of symptom severity than can be obtained with any single measure alone. Conceptually or procedurally related indicators (eg, fatigue-related items, BCBT variables, and MRI measures) will be modeled to account for residual correlations by including terms describing local dependence. This is performed to avoid inflating latent factor loadings or identifying spurious subgroups driven by unmodeled shared variance. In the LCA analyses, observed variables will be treated as indicators of an underlying categorical latent variable. Patients will thus be grouped according to their multivariate response profiles. The number of classes will be estimated using information criteria (Akaike information criterion and Bayesian information criterion) and by excluding solutions with very small or clinically uninterpretable classes. Given the limited sample size, we will restrict models to a maximum of four classes. For each class, we will estimate the expected response pattern and assess whether the resulting classes have meaningful clinical interpretations. Associations between latent outcomes and external covariates, such as age and sex, will be examined post hoc, with covariates treated as external variables rather than incorporated directly into the latent variable models. This includes assessing whether patients are exercise-intolerant, defined by both clinical criteria and self-reported experience. Finally, we will extend the models to incorporate both baseline and follow-up data. In the SEM analyses, we will estimate the effect of the intervention on the latent PPCS construct, while in the LCA analyses, we will test whether the intervention effect differs across latent classes.

Statistical modeling will be handled externally at the Institute for Biostatistics, University of Copenhagen. In this large study, we have included other a priori defined measures of distinct types, and therefore, further testing will be performed. We treat these tests as hypothesis-generating for further studies and consider that corrections for multiple testing are irrelevant, as discussed previously [46,47].

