## Introduction

### Background

Persistent postconcussion symptoms (PPCSs) may develop in some individuals after mild traumatic brain injury (mTBI) [1,2], and mTBI can be used interchangeably with “concussion,” as defined by the American Congress of Rehabilitation Medicine in 2023 [3,4]. The symptoms represent a complex phenomenon causing a broad spectrum of issues, including musculoskeletal and balance disturbances, cognitive impairments, visual and auditory dysfunctions, fatigue, and headache-related problems [5]. Adults with PPCSs frequently demonstrate increased sensitivity to physical, cognitive, and perceptual stimuli, which can substantially impair their capacity to engage in physical activity, participate in social interactions, sustain full-time employment, and pursue or complete higher education [6].

In Denmark, approximately 30,000 to 40,000 adults experience traumatic brain injury (TBI) annually, with more than 80% of cases being classified as mTBI [6,7]. However, this number is likely underestimated owing to underreporting and the fact that only hospital contacts are included in the epidemiological statistics. Within the subset of approximately 25,000 individuals with mTBI, 40% experience symptoms persisting beyond 4 weeks, and up to 15% continue to experience symptoms up to a year or longer after the initial concussion [6]. A nationwide cohort study identified 19,732 adults aged 18‐60 years with hospital-diagnosed mTBI over 5 years from 2003 to 2007, and found that 43% of the individuals were not engaged in full-time employment 5 years after mTBI [6].

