### Randomization and Blinding

Randomization to either the TG or the CG occurred after completion of the clinical screening examination and followed a 1:1 allocation ratio. Because PPCSs are more prevalent among women than men, an equal sex distribution was not anticipated; however, the allocation ensured an equal number of patients with PPCSs in each group. The randomization sequence was generated by [name], who was not involved in any other aspect of the trial, including patient recruitment, assessment, intervention delivery, data management, or analysis, thereby maintaining independence and minimizing the risk of allocation bias. The sequence was produced a priori using a computer-generated randomization list created through an online tool provided by Sealed Envelope. Allocation was implemented according to this pregenerated list, ensuring that those responsible for enrolling patients and assigning them to groups had no access to the randomization sequence prior to assignment, which is in line with SPIRIT recommendations for allocation concealment.

For all baseline assessments in subproject 2 (physiological evaluation), the tester was blinded to group allocation. The tester was also blinded to group allocation for all 12-week follow-up assessments. In addition, different testers conducted the baseline and 12-week follow-up assessments. Furthermore, the personal trainers supervising the exercise sessions were different from all the testers.

In subproject 3 (neurofunctional evaluation), which involved collecting and analyzing MRI data, a blinding protocol was strictly followed. The project staff handling and analyzing the MRI data were unaware of the participants’ group allocations. Similarly, the project leaders and statisticians were blinded to group allocations in the dataset used for the physiological and neurobiological analyses.

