### Physical Tests

All participants completed a multimodal battery of physiological tests (Table 1) at baseline and the 12-week follow-up. Since all participants had completed a subjective symptom profile assessment and a basic neurological test at screening, the purpose of the physical test was to cover relevant physical, oculomotor, balance, autonomic, and cervical aspects of PPCSs through objective measures prior to the validated BCBT [14]. The BCBT determined the individual HR threshold at which concussion-specific symptom exacerbation occurred and outlined the structure for the 12-week training program in the TG.

**Table 1. T1:** Overview of data collection, prescreening, clinical screening, and physiological tests in the study.

Variable	Week 0	Week 4	Week 8	Week 12
Prescreening phone interview				
Trauma description	✓	—^a^	—	—
Symptoms reported at prescreening	✓	—	—	—
Job situation	✓	—	—	—
Clinical screening				
Neurological examination	✓	—	—	—
Symptoms described at screening	✓	—	—	—
Irritability	✓	—	—	—
Cervical spine subjective description	✓	—	—	—
Headache description	✓	—	—	—
Vestibular and oculomotor	✓	—	—	—
Symptoms beyond physical issues	✓	—	—	—
Physical activity	✓	—	—	—
Physiological tests				
Posture	✓	—	—	✓
VAS^b^ (beginning of the test)	✓	—	—	✓
Cervical range of motion	✓	—	—	✓
Cervical safety test	✓	—	—	✓
Tendon reflexes	✓	—	—	✓
Dynamic Gait Index	✓	—	—	✓
Smooth pursuit for nystagmus	✓	—	—	✓
Repetitive saccades	✓	—	—	✓
Fatigue Severity Scale	✓	—	—	✓
VAS inverse	✓	—	—	✓
RPQ^c^	✓	✓	✓	✓
Orthostatic blood pressure	✓	—	—	✓
VAS (before the BCBT^d^)	✓	✓	✓	✓
Extended description of VAS	✓	—	—	✓
BCBT	✓	✓	✓	✓
Time cycled	✓	✓	✓	✓
Watt (end of the test)	✓	✓	✓	✓
Pulse rate (end of the test)	✓	✓	✓	✓
Rate of perceived exertion (end of the test)	✓	✓	✓	✓
VAS (end of the BCBT)	✓	✓	✓	✓

a Not applicable.

b VAS: Visual Analog Scale.

c RPQ: Rivermead Post-Concussion Symptoms Questionnaire.

d BCBT: Buffalo Concussion Bike Test.

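### The primary model leaves out time since injury, a plausible predictor of 12-week change, and enters age and sex in a form that cannot sharpen the Group × Time estimate; prespecifying it is a cheap gain in precision, not the repair of an error

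*Protocol article*

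**What the plan says.** The Statistical Analysis section of the protocol article prints the primary model in full. The outcome is minutes on the Buffalo Concussion Bike Test (BCBT) until symptom provocation, before and after the intervention. The terms are Group, Time, Group × Time, Age, Sex and a random participant intercept. On the covariates it says: "Sex and age may influence these results, and they will be included as fixed effects". On the interaction: "This interaction term will provide the main result of the RCT study".

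Time since injury appears in neither this model nor the other models of that section. Textbox 1 admits patients whose symptoms have lasted more than 4 weeks after trauma and states no upper limit; it also admits patients with one or more injuries.

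Randomization and Blinding describes 1:1 allocation: "The sequence was produced a priori using a computer-generated randomization list created through an online tool provided by Sealed Envelope". No stratification by time since injury is described there.

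On natural course, the Background says of people with mild traumatic brain injury that "40% experience symptoms persisting beyond 4 weeks, and up to 15% continue to experience symptoms up to a year or longer" after the concussion. Table 1 lists "Trauma description" among the items collected at prescreening.

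**The concern.** The primary result is a difference between arms in 12-week change. The protocol chooses its covariates because they may influence the result, yet its only figures on natural course concern time since injury, which is not among them. A patient who enters at 5 weeks and one who enters years after the injury are both eligible, and it is plausible that their expected 12-week change differs.

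The two covariates that are included enter as main effects. They shift a participant's level at both visits alike, so they cannot explain differences in change, and change is what the Group × Time term compares.

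At stake is the precision of the primary estimate, and how far an uneven split of recently injured patients between two arms of 35 could move it in this one trial.

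**Working it through.** **1. The plan's own figure.** From Sample Size Calculation: difference 6 min, SD 6 min, two-sided 5%, power 90%. A two-sample calculation gives 22 per group (noncentral-t power 0.900), which agrees with the plan: "With a 2-sided type 1 error rate of 5% and a statistical power of 90%, at least 22 participants were required in each group". With 70 patients and 30% dropout, 49 remain, or 24 per group rounded down; power for 6 min is then about 0.93 without any further covariate.

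**2. What the persistence figures give.** Of those symptomatic at 4 weeks, 1 − 15/40 = 62.5% resolve by one year. The average weekly hazard is −ln(0.40)/4 = 0.229 over weeks 0–4 and ln(40/15)/48 = 0.020 over weeks 4–52. Resolution therefore slows with time, which makes time since injury a plausible predictor. These are symptom figures at two time points; they contain nothing on BCBT time.

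**3. What main effects do.** With complete pre and post data, a covariate that is constant within a participant cancels from post minus pre, so the Group × Time estimate equals the raw difference in mean change. In one simulated complete-data trial the estimate was 1.134 with no covariate, with age, and with age plus time since injury, identical to the difference in change scores. It moved, to 1.147, only when a time-since-injury × Time term was added.

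**4. Bias and type I error.** Simulation of the stated model under no treatment effect (35 per group, 30% dropout at random, 150 runs per scenario) gave mean estimates between −0.10 and 0.01 min and rejection rates of 3–7%, compatible with 5%.

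**5. Chance imbalance.** Let p be the share of recently injured patients (assumed). The between-arm difference in that share has SD √[2p(1 − p)/n]. For p = 0.5 the 95% limit is 1.96 × 0.1195 = 0.23 with n = 35 and 1.96 × 0.1443 = 0.28 with n = 24. Multiplied by an assumed gap in natural gain between recent and long-standing cases:

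| Gap (assumed) | 35 per group | 24 per group |
|---|---|---|
| 3 min | 0.70 min | 0.85 min |
| 6 min | 1.41 min | 1.70 min |

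**6. Variance saved.** Take the SD of change as 6 min (assumed; the plan's 6 min is a common SD for the group comparison). The share of variance explained is p(1 − p) × gap²/36:

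- gap 3 min: 0.21 × 9/36 = 5.3% (p = 0.3) to 0.25 × 9/36 = 6.3% (p = 0.5);
- gap 6 min: 0.21 × 36/36 = 21% to 0.25 × 36/36 = 25%.

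Estimating one more slope in the comparison of changes costs about 1/67 = 1.5% with 70 patients and 1/46 = 2.2% with 49 completers. Simulated variance ratios (adjusted to unadjusted, 6,000 trials each, 24 or 35 per arm) were 0.96–0.97 for 3 min, 0.76–0.82 for 6 min, and 1.02–1.03 for a useless covariate. The saving is thus roughly 3% to 25%.

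**7. The continuous form.** In the simulations of step 4, a normally distributed covariate standing for log(time since injury) changed the 12-week gain by 0, 1.5 or 3 min per SD (assumed). Adding its interaction with Time moved the mean standard error of the Group × Time term from 1.37 to 1.39, 1.43 to 1.39, and 1.57 to 1.38. As variances, these are a 3% loss, a 6% saving and a 23% saving. The main effect alone left the standard error at 1.38, 1.43 and 1.57.

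**The case against.** The strongest reply is that no error is shown. In a 1:1 randomized comparison, omitting a prognostic covariate leaves the estimate unbiased, and which covariates to prespecify is a matter of judgement. Chance imbalance is not an extra error: the standard error already covers it. With SD 6 and 35 per arm the 95% half-width is 1.96 × 6 × √(2/35) = 2.8 min, and the shifts in step 5 lie inside it. Power is already about 93% at the planned effect. All of this stands.

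A reader might go further and infer that the persistence figures show time since injury to govern change in BCBT time, and might put minutes on it: a constant hazard of 0.020 per week gives about 22% resolving in any 12 weeks, and 22% of the 27.2 − 14.6 = 12.6 min deficit is 2.7 min. The documents do not support this. A constant hazard has no memory, so it implies the same expected recovery for entry at 5 or at 30 weeks; a gap appears only if recovery in long-standing cases is set to zero. The conversion also assumes that every patient whose symptoms resolve gains the full deficit and that nobody else gains anything. And the figures describe people with mild traumatic brain injury at large, whereas the trial recruited largely through referral networks, rehabilitation centers and a patient association.

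Feasibility is also less certain than it looks. The entry criterion needs only confirmation that 4 weeks have passed, Table 1 does not say that an injury date was recorded, and repeated injuries are allowed.

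None of this removes the case for the covariate. It limits the claim to precision and robustness, and makes the size an assumption.

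**Conclusion.** The point holds as a suggestion for improvement. The primary model adjusts only for age and sex, in a form that does nothing for the Group × Time term with complete data, and it omits a plausible predictor of change that the wide entry window leaves free to vary.

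A reader might infer that the omission biases the result or inflates the type I error. It does neither: allocation is randomized, and the simulated rejection rates are compatible with 5%.

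The gain is a variance reduction of roughly 3% to 25%, against a loss of about 1–2% if the covariate proves useless. That range rests on assumed gaps of 3 to 6 min, an assumed 30–50% share of recent cases and an assumed SD of change of 6 min; the protocol article gives none of these. The upper end needs a gap as large as the treatment target itself: "A between-group difference of 6 minutes was therefore defined as clinically meaningful".

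A secondary benefit concerns dropout. The plan allows for 30%, assumes data missing at random and uses no imputation. If dropout depends on time since injury, that assumption is better supported with the variable in the model.

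**What to change.** Before unblinding, add one sentence to the analysis plan in either of two forms:

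- keep the mixed model and add log(time since injury) together with its interaction with Time, because the main effect alone does not move the Group × Time term with complete data; or
- analyse the 12-week BCBT time by ANCOVA on the baseline value, with log(time since injury) as a further baseline covariate. In this form age and sex can contribute to precision as well. Participants without a 12-week value drop out of a simple ANCOVA, so it would have to be squared with the intention-to-treat set in the Missing Data section.

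Define the index injury from which time is counted, since patients may have had more than one, and confirm that its date can be taken from the trauma description or the medical documentation for every patient.

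The cost is one sentence and two degrees of freedom in the mixed model, about 1–2% of variance if the covariate explains nothing. The article says that the statisticians are blinded to allocation and that analysis is ongoing; the same adjustment chosen after unblinding would be post hoc.
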